### Variables

#### Exposures

For our primary analysis, we will define all exposures based on the first prescription observed in the database.^10^ This is so that the target parameter estimated in the observational study will be comparable to that estimated by a randomised controlled trial (RCT). Analogous to an intention-to-treat analysis in a RCT, patients initially prescribed an active treatment medication (exposed), but later stop that medication or switch to a control drug (unexposed), will be allocated to treatment (ie, classified as exposed, irrespective of what happens in the future) and vice versa. First time prescriptions of the medications of interest (treatment and control) will be defined as people who received at least one prescription of the product but who had no use of a related product during the 12 months before the start of follow-up. The prescriptions will be identified using product codes recorded in the therapy file in the CPRD, which details the date each prescription was issued, the quantity of drug prescribed and the dosage. Patients initially receiving more than one prescription of a drug of interest will be included in our analysis in a group representing the specific combination of drugs they receive. The effects of treatment switching and disease control will be explored using marginal structural models. We will also consider disease severity for the treatment indications through the use of instrumental variable analysis.

#### Outcomes

For incidence, we will identify the neurodegenerative disease outcomes (AD, NADD, PD and ALS) by the first record of a relevant read code (see online supplementary file 4) or the first record of a product code indicating treatment for the neurodegenerative disease (see online supplementary file 5). For incidence and progression, we will identify deaths using linked Office of National Statistics (ONS) data.

#### Covariates

We will match all covariates on date of birth, sex, year of index date and years of recorded history in the database before the index date. The covariates we will include in our analyses are body mass index, smoking status, alcohol consumption, a postcode-based measure of socioeconomic position, previous history of coronary-artery disease, previous coronary-bypass surgery and cerebrovascular disease including stroke. We will also control for other major chronic illness (including cancer, arthritis) using the Charlson Index^11^
^12^ and for consultation rate, calculated by dividing the total number of clinic visits prior to the index date by the length of each patient's follow-up. If there are missing data in the covariates, we will consider using multiple imputation. Unfortunately not all covariates of interest, such as exercise, are recorded within the CPRD, and this may lead to unmeasured confounding. We hope to minimise this confounding by using methods, such as instrumental variable analysis, which can account for it to some degree.

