### Confounding

We have identified two key sources of confounding in our study: confounding by indication and time-dependent confounding. To address the former, we will use four different statistical methods, which have different approaches for modelling confounding. Through examination of these approaches, we hope to highlight any uncontrolled confounding that may be leading to false conclusions about drug effect. We will also account for confounding by indication in the construction of our cohorts. Consider cohort A, where we compare ‘exposed’ and ‘unexposed’ groups of individuals. Drawing the ‘unexposed’ group from the full population can introduce bias as they are likely to be in better health. We will avoid this by defining cohort entry on the basis of first test or recording of a relevant read code so the ‘exposed’ and ‘unexposed’ groups will have more in common. In addition to this, we will address time-dependent confounding in our study. This will be carried out using marginal structural models, which can allow for time-dependent confounding and treatment switching between products.

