### Statistical methods

We will use four statistical approaches in our study—they are multivariable adjusted Cox regression, propensity matched regression, instrumental variable analysis and marginal structural models. We are committed to presenting the findings from all our analyses, irrespective of the direction of findings and will handle discrepancies between them by assessing the merits of each method in the given situation. If we discover large main effects of specific medications, we may investigate interactions between covariates and will seek to replicate any interactions in other large samples.

We will be using an intention to treat analysis in our primary analysis. The reasons for this are twofold. First, while there are theoretical statistical models for estimating the effects of treatment switching such as marginal structural models, these methods require the strong assumption that there are no unmeasured confounders. Second, to the best of our knowledge there are no instrumental variable methods for estimating the effects of treatment switching. We will investigate treatment switching using marginal structural models in a secondary analysis. All of the methods we will use for this study are summarised below.

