#### Multivariable adjusted Cox regression

In our first analyses, a conventional observational analysis, we will estimate the HRs of incidence and survival using Cox proportional hazards models. Both analyses will use the actual prescriptions issued to the patients.^20^ We will report these associations adjusted for basic confounders (age and gender) and results adjusted for all measured covariates described previously. We will also perform tests of the proportional hazards assumption.

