#### Propensity matched regression

In our second analysis, we will construct a sample of patients balanced on covariates and risk factors using a propensity score.^21–24^ We will construct propensity scores using a logistic regression of the actual treatment received on the covariates described above. Therefore, each participant's propensity score will be their conditional probability (odds) of receiving treatment or not (cohort types A and C), or receiving treatment versus control therapy (cohort type B). We will match each patient receiving one treatment to another patient receiving the control treatment with the closest propensity score on a ratio of 1:1 using a nearest neighbour algorithm with no replacement, and matching will be restricted to the common support region. Patients outside the common support region are those prescribed the treatment therapy with propensity scores higher than any patient prescribed the control treatment and vice versa. We will estimate odds ratios and HRs of the outcomes using the propensity score matched sample using logistic and Cox regressions.

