#### Marginal structural models

In our fourth analysis, we will estimate the effects of each treatment using marginal structural models.^32^ We will use these models to account for time-dependent confounding and treatment switching. We will construct inverse probability weights for each treatment based on the patients' observed characteristics such as gender, age, comorbidities and concurrent treatments. We will use these models to estimate the odds and HRs of disease incidence and progression.

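### The Cox and propensity models adjust for most comorbidity only through the Charlson Index, so avoidable confounding by indication can remain in these HRs

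*Protocol article*

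**What the plan says.** The Covariates section gives the adjustment set. Besides lifestyle factors, socioeconomic position and consultation rate, the only diseases entered by name are "previous history of coronary-artery disease, previous coronary-bypass surgery and cerebrovascular disease including stroke". Other illness follows in one sentence: "We will also control for other major chronic illness (including cancer, arthritis) using the Charlson Index".

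Two analyses take over this set. The Cox section promises "results adjusted for all measured covariates described previously". The propensity section says: "We will construct propensity scores using a logistic regression of the actual treatment received on the covariates described above".

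The Confounding section states the threat: "We have identified two key sources of confounding in our study: confounding by indication and time-dependent confounding". It relies on comparing four methods, and on the way the cohorts are built, to deal with it.

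The other two methods differ:
- Instrumental variable (IV) analysis reports risk differences, treats survival models as exploratory and, in Table 1, is listed for cohorts A and B but not for C.
- Marginal structural models (MSM) use weights built from "observed characteristics such as gender, age, comorbidities and concurrent treatments". The text does not say whether the comorbidities are separate terms or the index. For switching, these models are secondary: "We will investigate treatment switching using marginal structural models in a secondary analysis".

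**The concern.** A summary index gives two patients the same value whenever their totals agree, whatever illnesses produced the totals. If one of those illnesses influences which drug is started and also affects the outcome, adjusting for or matching on the total does not equalise it between drug groups.

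This matters most in two places. Cohort B compares subclasses by first prescription, so a single illness can tip the choice of drug. Cohort C compares treated with untreated patients on survival, without an IV analysis as a cross-check.

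The study is large and is meant to help prioritise drugs for trials. A residual bias of a few per cent could be statistically significant in the largest comparisons and be read as a drug effect. It would be avoidable bias, because the component conditions must be identified to compute the index.

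**Working it through.** **1. What each analysis uses**

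| Analysis | Comorbidity adjustment | Effect scale | Cohorts (Table 1) |
|---|---|---|---|
| Cox | Covariates list, with index | HR | A, B, C |
| Propensity matching | same list | OR, HR | A, B, C |
| IV | prescriber preference as instrument | risk difference | A, B |
| MSM | comorbidities and concurrent treatments, not itemised | odds, HR | A, B, C |

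The first two rows share the index, so their agreement says nothing about what the index hides.

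**2. Yardstick from the plan**

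Table 3 gives minimum detectable HRs of 0.968, 0.943 and 0.844 (cohort B: hypertension, hypercholesterolaemia and diabetes are 0.968, 0.844 and 0.943 respectively) and 0.931, 0.870 and 0.600 (cohort C: dementia, PD, ALS). The event rates and group shares behind them are in supplementary files not shown, so these figures can be neither reproduced nor refuted.

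The Schoenfeld formula, with 80% power and two-sided 5% (sidedness is not stated), shows what they imply: events × p(1−p) = (1.960 + 0.842)² / (ln HR)².
- HR 0.968: 7.849 / (0.0325)² ≈ 7420, or about 29 682 events at 1:1.
- HR 0.931: 7.849 / (0.0715)² ≈ 1535, or about 6142 events at 1:1.

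**3. Illustration with no drug effect**

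All inputs here are assumptions, none from the document:
- six independent, equally weighted conditions with prevalence 5–10%;
- one of them raises the odds of receiving the study drug by OR 2, 4 or 8;
- that condition has outcome HR 1.2, 1.5 or 2.0, and each of the others about 1.1;
- baseline hazard 0.008 per year over 6 years.

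Expected events and person-time were computed for all 64 condition patterns in each group. A Poisson hazard model was then fitted without adjustment, with the summed score, and with six separate terms. The true HR is 1.000.

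| OR | Outcome HR | Unadjusted | Score | Separate |
|---|---|---|---|---|
| 2 | 1.2 | 1.012 | 1.005 | 1.000 |
| 2 | 1.5 | 1.030 | 1.019 | 1.000 |
| 2 | 2.0 | 1.058 | 1.042 | 1.000 |
| 4 | 1.2 | 1.029 | 1.011 | 1.000 |
| 4 | 1.5 | 1.071 | 1.046 | 1.000 |
| 4 | 2.0 | 1.137 | 1.099 | 1.000 |
| 8 | 1.2 | 1.048 | 1.018 | 1.000 |
| 8 | 1.5 | 1.117 | 1.075 | 1.000 |
| 8 | 2.0 | 1.227 | 1.163 | 1.000 |

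Entering the score in categories gives the same values in this set-up. The share of bias removed is 1 − ln(score HR)/ln(unadjusted HR). It runs from about 26% (OR 8, HR 2.0) to about 61% (OR 2, HR 1.2).

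**4. Against the yardstick**

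1/0.968 = 1.033, and five of the nine score-adjusted HRs exceed it (1.042, 1.046, 1.099, 1.075, 1.163). 1/0.943 = 1.060, and three exceed it. 1/0.870 = 1.149, and one does. 1/0.844 = 1.185 and 1/0.600 = 1.667, and none does.

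**5. A second illustration with unequal weights**

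This was a simulation of 50 000 v 200 000 starters, about 8000 outcomes and 40 replicates per setting, again with no drug effect and assumed inputs. With one condition in 30% v 3% of starters and outcome HR 1.5, the score-adjusted HR was 1.12 (1.09–1.11 with the score in categories) and 1.00–1.01 with separate terms. At 15% v 3% it was about 1.05. At 10% v 5%, or with outcome HR 1.2, the residual was 0–4%.

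**The case against.** **The coding of the index is not spelled out.** The article does not say that one linear sum is used, and categories or component terms are not excluded. That is true. But controlling through an index is what the text states, and categorising it did not remove the residual in either illustration. This is a stated choice of covariates and not a detail left to a fuller plan.

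**The index's content comes from cited sources that are not shown.** No section says which illness steers a subclass, or that it is part of the index. This stands. If the decisive illness lies outside the index, splitting the index does not help.

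**The plan has other safeguards.** IV analysis does not depend on the index to balance illness between drugs, and it is planned for cohort B, where the concern is greatest. The plan is also committed to reporting every method. This stands in part: IV may expose a discrepancy in cohorts A and B, but on the risk-difference scale, and it is absent in cohort C. The MSM weights may already use separate comorbidities.

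**The larger figures need strong assumptions.** A prevalence of 30% v 3% is an odds ratio of (0.30/0.70)/(0.03/0.97) ≈ 14. Neither illustration includes the covariates the plan does enter separately, and correlation with them could shrink the residual. Also, 0.968 is the most sensitive of six rows in Table 3. The simulated contrast has events × p(1−p) = 8000 × 0.2 × 0.8 = 1280, so its own detectable HR is only exp(−2.802/√1280) ≈ 0.925. All of this stands.

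A reader might infer that the plan's HRs are all biased by some 10%. The documents do not support that. They contain no prevalences by drug group, and the point does not extend with certainty to the MSM HRs.

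**Conclusion.** The point holds for the Cox and propensity-matched HRs. Outside coronary and cerebrovascular disease, comorbidity is adjusted for only through a summary index, which cannot guarantee balance on a specific illness that drives prescribing. Some avoidable confounding by indication can remain, chiefly in cohort B and cohort C, and agreement between these two methods would not show it.

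The size is illustrative only: under the assumed inputs, from under 1% to over 10%, and small when imbalance is modest. The direction depends on whether the illness is commoner in the study-drug or the comparison group and on how it relates to the outcome, neither of which the document gives. Propensity matching was not simulated; that part rests on its using the same covariate list.

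This is a cheap improvement worth making before analysis. It does not show that the planned results would be wrong.

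**What to change.** In the Cox and propensity models, replace the Charlson Index with a separate yes/no covariate for each of its component conditions. Do the same in the MSM weights if they use the index, and state in the Marginal structural models section which comorbidity terms the weights contain. Report balance on each condition by drug group, in cohort B by subclass. Keep the index for description or as a sensitivity analysis.

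Group rare conditions in the ALS (2227) and PD (20 686) cohorts and in subclasses with few exposed patients. The caution for subclasses is real: the stated HR of 0.844 for hypercholesterolaemia implies events × p(1−p) of only about 7.849/(0.1696)² ≈ 270.

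The cost is a few more model terms and some sparse cells in the small groups. No new data are needed, since the components have to be coded to compute the index.

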Start of follow-up (index date)	Date at first risk of the condition the treatment is used for or date of first diagnosis of the condition itself if there was no preceding period ‘at risk’.	Date of first prescription of a treatment of interest.	Date of first diagnosis of neurodegenerative disease of interest.
Outcome	Diagnosis of neurodegenerative disease of interest.	Diagnosis of neurodegenerative disease of interest.	Death.
Exclusion criteria	Individuals with <12 consecutive months of records prior to cohort entry.	Individuals prescribed treatment and control medications at the same time or with <12 consecutive months of records prior to cohort entry.	Individuals with <12 consecutive months of records prior to cohort entry.
Statistical analysis	Conventional regression, propensity score regression, instrumental variable analysis and marginal structural models.	Conventional regression, propensity score regression, instrumental variable analysis and marginal structural models.	Conventional regression, propensity score regression and marginal structural models.

AD, Alzheimer's disease; ALS, amyotrophic lateral sclerosis; NADD, Non-Alzheimer's disease dementias; PD, Parkinson's disease.

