**Figure 1 BMJOPEN2016012044F1:**
[figure not shown]
The cohort construction for cohort type A, designed to eliminate immortal time bias. A patient will enter the cohort for a given treatment when they first become ‘at risk’ of the condition the treatment is used for or, in the case of no period ‘at risk’, when they are first diagnosed with the condition (see table 2). For example, when they are diagnosed as at ‘at risk of’ hypertension or, in the case of no period ‘at risk’, when they receive a diagnosis of hypertension. We define cohort entry in this way to avoid excluded immortal time bias that can occur when cohort entry is determined by treatment variation over time.^33^
^34^ Immortal time is the period during follow-up when the outcome cannot occur. Consider the hypertension example above, suppose we started following the treated patients in our cohort from the date of their first prescription of a treatment for hypertension and the untreated patients from a matched date. This would make it impossible for the treated patients to have an outcome, such as dementia, prior to their first prescription. Consequently, patients in this group would all have a period before treatment, when they could not be diagnosed with dementia, that is, they could not experience the outcome. This period is their immortal time, and it must be correctly attributed to the ‘unexposed’ group so that their outcome is not falsely attributed to their exposure. To do this, patients in the ‘exposed’ and ‘unexposed’ groups must be followed-up and compared from the same start date. In this cohort, we are minimising excluded immortal time by following patients from either a test result or diagnosis where possible. In order to capture all relevant patients, we will allow those receiving treatment without a recorded diagnosis to be included as it is assumed treatment suggests a diagnosis.

10.1136/bmjopen-2016-012044.supp1supplementary file

10.1136/bmjopen-2016-012044.supp2supplementary file

10.1136/bmjopen-2016-012044.supp3supplementary file

Follow-up for cohort A will start on the first date a patient is diagnosed with the condition the treatment is used for or ‘at risk’ of that condition (see table 2 and online supplementary files 1–3.) Follow-up will end with the earliest of a relevant neurodegenerative disease diagnosis, death or censoring due to the end of registration at a CPRD general practice.

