#### Cohort B

In this analysis, we will compare different drug subclasses that exist for a given treatment (listed in box 1). To do this, we will create a cohort of all patients who were prescribed a treatment and categorise them by the drug subclass they initially received. This will allow us to compare the outcomes for each of the resulting subgroups. For each treatment, we have defined the most frequently prescribed subclass as the control (indicated in box 1). In the primary analysis of this cohort, we will exclude patients initially prescribed the control subclass if they receive another subclass of the same treatment at the same time, however we do not expect this to be a common. We will explore the outcomes of individuals prescribed multiple subclasses, other than that specified above, in a sensitivity analysis.
Box 1The drug subclasses of interest for each treatment group with the control treatments indicatedTreatments for hypertensionBeta-adrenoceptor blocking drugs (control)Angiotensin-converting enzyme inhibitorsThiazides and related diureticsCalcium channel blockersLoop diureticsAlpha-adrenoceptor blocking drugsCentrally acting antihypertensive drugsAngiotensin-II receptor antagonistsVasodilator antihypertensive drugsPotassium-sparing diuretics and aldosterone antagonistsTreatments for hypercholesterolaemiaStatins (control)FibratesBile acid sequestrantsOmega-3 fatty acid compoundsEzetimibeNicotinic acid groupTreatments for type 2 diabetesBiguanides (control)SulphonylureasOther antidiabetic drugs

Follow-up for cohort B will start on the date of first eligible prescription as determined by a product code (see the treatment code lists in online supplementary files 1–3). Follow-up will end with the earliest of a relevant neurodegenerative disease diagnosis, death or censoring due to the end of registration at a CPRD general practice.

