#### Cohort C

For each neurodegenerative disease group of interest, we will create a cohort of individuals with a read code indicating this outcome (see online supplementary file 4) or a product code indicating they received treatment for the outcome (see online supplementary file 5). These cohorts will be used to investigate the associations of neurodegenerative disease progression with exposure to one of the three treatment groups of interest: treatments for hypertension, treatments for hypercholesterolaemia and treatments for type 2 diabetes. We will investigate both exposure before and after the diagnosis of a neurodegenerative disease. For all of the treatments we consider, each cohort will be split into ‘exposed’ and ‘unexposed’ groups. In the analysis, individuals in the ‘exposed’ group, that is, those who were prescribed the treatment under investigation, will be compared with individuals in the ‘unexposed’ groups, that is, those who did not receive the treatment.

10.1136/bmjopen-2016-012044.supp4supplementary file

10.1136/bmjopen-2016-012044.supp5supplementary file

Follow-up for cohort C will start with the first recorded read code indicating AD or other neurodegenerative disease (see online supplementary file 4) or, in the absence of a diagnosis, the first recorded product code indicating they received treatment for a neurodegenerative disease (see online supplementary file 5). Follow-up will end with the earliest of death or censoring due to the end of registration at a CPRD general practice.

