### Bias

There are three main sources of bias in our results: ascertainment bias, collider bias and immortal time bias. To overcome ascertainment bias, we will control for consultation rate in our analyses because people who have more chronic conditions such as hypertension, diabetes or renal insufficiency may have higher rates of consultation, which may also increase the opportunity for recording other diagnoses such as dementia. Collider bias could occur if we conditioned on events that happened as a result of the prescription the patient was issued. To prevent this form of bias from affecting our results, we will define each covariate using data inputted prior to the index date.^14^ Finally, we will minimise the risk of immortal time bias in two ways. First, to prevent misclassified immortal time, we will define exposures based on the first prescription observed in the database^10^ and use an intention-to-treat analysis. Second, to minimise immortal time, we will follow-up patients (exposed and unexposed) from a consistent index date. This will be a test result or a read code indicating diagnosis where possible;^15^ however, to capture all relevant patients, we will allow those receiving treatment without a recorded diagnosis to be included.

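### Consultation rate is defined with post-index follow-up as its denominator, which puts observed survival time into the fully adjusted Cox model and the propensity score and breaks the protocol's own pre-index rule

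*Protocol article*

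**What the plan says.** The Covariates section says the analyses will control for consultation rate, "calculated by dividing the total number of clinic visits prior to the index date by the length of each patient's follow-up". The Bias section gives its purpose: "To overcome ascertainment bias, we will control for consultation rate in our analyses". The same paragraph sets a rule for all covariates in order to avoid collider bias: "we will define each covariate using data inputted prior to the index date".

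The article gives follow-up one meaning. The Table 1 row label ties its start to the index date ("Start of follow-up (index date"). The cohort sections then say:

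- Cohort A, start: "Follow-up for cohort A will start on the first date a patient is diagnosed with the condition the treatment is used for", or is first at risk of it. End: "Follow-up will end with the earliest of a relevant neurodegenerative disease diagnosis, death or censoring due to the end of registration".
- Cohort B, start: "Follow-up for cohort B will start on the date of first eligible prescription". The end is the same as in cohort A.
- Cohort C starts at the first record of the neurodegenerative disease. End: "Follow-up will end with the earliest of death or censoring due to the end of registration at a CPRD general practice".

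The Cox section reports one model adjusted for age and gender and one adjusted for all measured covariates. The propensity section builds the score from the same covariate list.

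**The concern.** The numerator is counted before the index date and the denominator is measured after it. For a patient who has the event, the denominator is the event time that the Cox model analyses; for the others it is the censoring time. A short time to event gives a large value whatever the patient's consulting habit, so the variable looks strongly prognostic even if consulting has no effect on outcome.

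The drug estimate is then at risk. If exposed patients made more visits before index, or were followed for less time, they carry higher values for reasons unrelated to hazard, and the exposure coefficient shifts to compensate. The Bias section itself expects patients with more chronic conditions to consult more. With more visits among the exposed, a drug with no effect would look protective, which is the effect the study is looking for. In the propensity score, the same variable would let matching depend on what happened after index.

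**Working it through.** **1. Text.** No stated sample size or detectable HR depends on this covariate, so there is no plan figure to reproduce. Numerator: visits before index. Denominator: index date to end of follow-up (Table 1; Cohort A, B and C sections). The Bias section allows only pre-index data. These statements cannot all hold.

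**2. Arithmetic.** Take 60 visits over 10 pre-index years.

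- Pre-index rate: 60/10 = 6 per year.
- Stated formula with 1, 5 or 10 years of follow-up: 60/1 = 60, 60/5 = 12, 60/10 = 6.

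Identical consulting gives a tenfold range, with the highest value for the shortest follow-up.

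**3. Simulation on the log scale.** There were 6,000 patients and 6 replicates per scenario. The following are assumed and not in the article: pre-index history uniform on 1–15 years, about 5 visits per year, censoring uniform on 0.1–15 years, and outcome hazard 0.02 or 0.2 per year. True drug HR is 1.0, and visits have no effect on outcome.

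| Visit-rate ratio, exposed:unexposed | Hazard | HR unadjusted | HR, pre-index denominator | HR, stated denominator | Covariate HR per log unit, stated |
|---|---|---|---|---|---|
| 1.00 | 0.02 | 0.989 | 0.990 | 1.022 | 3.336 |
| 1.00 | 0.2 | 1.013 | 1.013 | 1.017 | 3.064 |
| 1.37 | 0.02 | 0.977 | 0.977 | 0.670 | 3.606 |
| 1.37 | 0.2 | 0.999 | 1.000 | 0.698 | 3.240 |
| 1.66 | 0.02 | 1.045 | 1.061 | 0.531 | 3.745 |
| 1.66 | 0.2 | 1.014 | 1.023 | 0.541 | 3.397 |

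With the pre-index denominator, the covariate HR is 0.97–1.00 in these six scenarios. With a true drug HR of 0.8, the stated denominator gives 0.81–0.82 (equal visit rates), 0.54–0.61 (ratio 1.37) and 0.41–0.46 (ratio 1.66). The pre-index denominator gives 0.77–0.82.

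**4. Hand check.** If the covariate has spurious log HR b and the exposed have a visit rate r times higher, the drug log HR should shift by about −b × ln(r).

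- r = 1.368, b = ln 3.606 = 1.283: exp(−1.283 × 0.313) = 0.67 (simulated 0.670).
- r = 1.368, b = ln 3.240 = 1.176: exp(−1.176 × 0.313) = 0.69 (simulated 0.698).
- r = 1.661, b = ln 3.397 = 1.223: exp(−1.223 × 0.507) = 0.54 (simulated 0.541).

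**5. When consulting does matter.** With visit propensity truly related to hazard (true drug HR 1.0, ratio 1.37, hazard 0.02), the unadjusted HR is 1.170. The pre-index denominator gives 1.023 and the stated one 0.762, so the stated version overshoots.

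**6. Other covariate scales.** A separate null simulation (40,000 patients, 3 replicates, 1% per year outcome, 3% per year death, follow-up under 3 months excluded) used 4 versus 6 pre-index visits per year. The HR moved from 1.00 to 0.93 (raw ratio), 0.77 (capped at the 99th percentile) and 0.64 (log). With maximum follow-up of 15 versus 6 years between groups, it moved from 1.05 to 0.95, 0.81 and 0.64. Without the 3-month exclusion, the raw-scale fit failed in three of four scenarios. The step 3 simulation could not fit the raw scale, and the unequal-follow-up scenario was not repeated. Propensity matching was not simulated; that part rests on reasoning.

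**The case against.** The best defence is that this is a drafting slip. The numerator is explicitly pre-index, the Bias section names the collider risk and rules out post-index data, and the Covariates section already lists a natural pre-index denominator, the years of record before index. This carries weight as evidence of intent. A reader might infer that the authors chose to adjust for survival time, and the article does not support that. But nowhere does it use follow-up for pre-index time, and an analyst coding the sentence would produce the faulty variable. Nor is this a detail left to a fuller document, because the article gives an explicit formula.

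A reader might also infer that every adjusted analysis is affected. It is not so: the age-and-gender Cox model omits the variable, the instrumental variable section lists no covariates, and the marginal structural section does not name it among the inputs to the weights.

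The sizes are open to fair challenge. The article specifies a plain ratio, with no log, cap or minimum follow-up. The visit rates and follow-up contrasts are assumed. The article also plans matching on index year and length of record, which the simulations did not include and which could narrow differences in follow-up. The 1.05 starting value under a true null may reflect simulation error with three replicates. All of this limits the numbers but does not rescue the formula.

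**Conclusion.** The formula is wrong as written and contradicts the Bias section. It affects the fully adjusted Cox model and the propensity score. The bias in the drug HR is conditional: with equal visits and equal follow-up it is small (null HR about 1.02), and it appears when the groups differ in either.

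The direction is well supported on the log scale: under the null, with more visits among the exposed, two simulations gave 0.64–0.70 at visit-rate ratios of 1.37 to 1.5 (6/4). On the raw scale, the one the article states, the only figure is 0.93, from one run that was not reproduced and that needed a 3-month exclusion. For context, Table 3 gives a minimum detectable HR of 0.931 for dementia in cohort C, so even that shift would matter if it held. A reader might take 0.64 as the expected error in this study. The documents do not support that, because it depends on assumed visit rates, a log scale and exclusions that the article does not contain.

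**What to change.** Define consultation rate as clinic visits before the index date divided by the patient's years of record before that date, a quantity the Covariates section already names. Alternatively, count visits in the 12 months before index, which the Table 1 exclusion criterion guarantees for every patient. Either makes the Covariates and Bias sections agree. If the intended denominator was pre-index time all along, say so explicitly.

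The cost is one sentence and one line of code. No new data are needed, and no stated sample size or detectable HR changes.
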